### Recruitment

**Participants**: Participants identified as having had surgery and discharged with opioids (<120 mg) within the last 7 days via participating GP practice sites undertaking weekly database searches and/or by screening discharge letters will be contacted by either an email or text, inviting them to participate in the study and providing a link to the patient information leaflet (PIL). Invited participants will then be contacted by the practice using a consecutive sampling approach via telephone within 48 hours of the invite being sent, asking if they would like to take part in the study, answering any questions and confirming their eligibility. For patients that agree to participate, an MUR appointment (online, telephone or in person) will be arranged with the pharmacist and a link to an online consent form sent to the participate to complete.

**Sample size:** A sample size of 80 – 100 participants will be recruited. Statistically, sensitivity power analyses have confirmed that the proposed number is able to detect significant differences of the expected effect size and is in line with the recommended sample size of 70 to estimate key parameters, bench-marked from external pilot randomised controlled trials
^
40
^ and will allow for participant loss, to follow-up.

**GP practices:** By utilising networks locally an Expressions of Interest document was circulated to GP practices in Kent. Further to this, research active practices in East Kent and South Kent were approached directly and capacity and capability assessed. Moreover, the project’s Clinical Lead contacted clinical pharmacists who had interest in, or experience in research of opioids or pain, to invite them to express interest in recruiting via their practice(s).

**Clinical pharmacists:** GP practice-based clinical pharmacists with experience of delivering MURs and opioid deprescribing will be recruited from participating practices. The clinical pharmacist/s will receive detailed information about the study, undergo some training with the study Clinical Lead and will be asked to provide written informed consent.

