### Surgical opioid use

Opioids are routinely used pre-, intra-, and post-surgically for the treatment of acute pain and post-operatively for pain management and is a primary route to exposure to these types of medicines, often for the first time
^
14,
15
^. Evidence from the US and Canada has shown a clear link between post-surgical opioid prescribing for both minor and major surgery, and persistent long-term use in the community, beyond tissue healing. Inappropriate prescribing of opioids both peri- and post-operatively, accounts for 36.5% of all opioid prescribing in the US, with 3 – 10% of these patients transitioning to long-term use
^
11,
14,
16,
17
^. Patients undergoing surgery are almost four times more likely to be discharged with opioids than their non-surgical counterparts
^
18
^. This is often with more opioid medication than is actually required to treat post-surgical pain
^
19–
22
^. Perhaps more alarmingly, almost half (45%) of these patients are given opioids even though they would not have been taking any opioids at point of discharge
^
23
^. In the United States (US), a study showed that between 5.9 – 6.5% of all patients who underwent surgery (versus 0.4% of the non-surgical control) went on to become long-term opioid dependent, even if they had never taken opioids before
^
15
^.

It is becoming clear from the US, that postsurgical prescribing of opioids is a problematic, underexplored, new source of long-term opioid use
^
17
^. Compared to the US and Canada, less is known in the UK about peri-operative opioid prescribing in hospitals and any link to long-term use. Two recent studies in the UK have identified long-term opioid use (>1 year) to be associated with older age (>75 years), being socioeconomically disadvantaged, having a history of depression and/or alcoholism, prior gapapentinoid or psychotrophic use, and those initiated on >120 morphine milligram equivalents (MME) following major surgery
^
6,
24
^. There are over 5.6 million opioid prescriptions dispensed each year in the UK, corresponding to around 13% of the adult UK population
^
25
^ and over 4.7 million surgical procedures occurring each year
^
26
^ and nearly 8 million people on surgical waiting lists, with over 300,000 waiting more than 52 weeks for surgery
^
27
^. This, along with no current national guidelines on peri-operative opioid prescribing, a declining GP workforce and increasing patient numbers
^
28

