### Consent process

Consent to participate in the study will be sought from all
eligible patients that have undergone a surgical procedure and are discharged with an opioid prescription from the participating East Kent hospital sites and participating GP practices. Consent will only be sought after a full explanation and/or the PIL has been offered with time allowed for questions and proper consideration. Individuals willing to take part and for whom an MUR appointment has been made will be asked to complete a Participant Consent Form. A Consent form will be sent to those with digital capabilities prior to the MUR or completed together with the pharmacist at the first appointment. A typewritten signature or tick box declaration option, in accordance with the UK eIDAS Regulations (SI 2016/696) will be used for all digital consent forms. All consent forms will be checked and countersigned by the pharmacist prior to the commencement of the medication review. A copy of the consent form will be added to the participants medical records, and another retained in the study site folder, stored at the practice and a copy sent to the participant.

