### Sources of bias

All potential eligible participants will be approached using emails or SMS text and followed up by telephone and the intervention delivered mainly by video or telephone. This will introduce selection bias towards those participants who are technologically adept. In addition, by restricting eligibility to participants that are taking opioids less than 120 mg/MME day, we are biasing our selection towards potentially less medically complex patients.

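### Email or text is the only described first contact, so eligible patients with neither have no described way in; the protocol discloses this selection bias but does nothing to reduce it, and a telephone fallback would be cheap

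*Protocol article*

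**What the plan says.** Four parts of the protocol article bear on this.

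- **Recruitment, Participants.** Practices identify patients by weekly database searches or by screening discharge letters. Those identified "will be contacted by either an email or text, inviting them to participate in the study and providing a link" to the patient information leaflet. The next step is: "Invited participants will then be contacted by the practice using a consecutive sampling approach via telephone within 48 hours of the invite being sent". Those who agree get a medicines use review (MUR) appointment, which may be online, by telephone or in person, and "a link to an online consent form sent to the participate to complete".
- **Sources of bias.** The same sequence is stated for everyone: "All potential eligible participants will be approached using emails or SMS text and followed up by telephone". The article adds: "This will introduce selection bias towards those participants who are technologically adept". No countermeasure follows.
- **Consent process.** Consent is to be sought from all eligible patients, after a full explanation, an offer of the leaflet, or both. The form "will be sent to those with digital capabilities prior to the MUR or completed together with the pharmacist at the first appointment".
- **Introduction, Surgical opioid use.** Two UK studies found long-term use (beyond one year) to be "associated with older age (>75 years), being socioeconomically disadvantaged", alongside several other factors.

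Table 1 lists, as feasibility measures, the number who accept an early MUR set against the number asked and, separately, the number of possible surgical participants per week.

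**The concern.** The later steps of the pathway can serve a patient who does not use email or text. The entry step, as described, does not reach that patient, because the telephone call is a follow-up to the electronic invitation and not an alternative first contact. The sampling is therefore consecutive among those invited, not among those eligible.

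This matters because of what the study is for. It is meant to inform a much larger trial, and Table 3 lists risk factors for long-term use and the transferability of the protocol among its outcomes. If the patients without a digital contact are older or more deprived than the rest, the case mix, the shares in the three pathways and the 91-day results would lean towards easier-to-reach patients. Uptake would describe digitally contactable patients only, since those never asked are in neither its numerator nor its denominator.

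**Working it through.** The plan gives no figure for this point, so there is nothing to reproduce. The check is mainly textual, followed by an illustration of size.

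**1. Is there any other first contact?** Recruitment describes email or text and no other invitation. The telephone call is restricted to invited patients and timed from the sending of the invitation. Sources of bias applies the same order to all potentially eligible patients. No postal, in-person or telephone-first invitation appears.

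**2. Do the later steps need a digital contact?** No. The practice telephones every invitee anyway, the MUR can be by telephone or in person, and consent can be completed with the pharmacist. Recruitment, however, mentions only an online consent link, which is narrower than the Consent process section.

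**3. Does the consent rule allow a verbal approach?** Yes. A full explanation is one of the accepted bases for seeking consent, with time for questions and consideration.

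**4. Is there time?** A weekly search covers the last 7 days and the call follows within 48 hours, so a patient found on day 7 may be called on day 7 + 2 = 9. The first MUR is due within ten days of discharge, which leaves one day. A telephone approach fits; a posted leaflet may not.

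**5. Illustration of size.** All inputs are assumptions; the documents give none of them:

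- share of eligible patients over 75, *p* = 20% to 30%
- share of those with neither email nor mobile, *a* = 20% to 40%
- the same share among younger patients, *b* = 2% to 5%

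Never invited = *p·a* + (1 − *p*)·*b*

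- Low: 0.2 × 0.2 + 0.8 × 0.02 = 0.056, or 5.6%
- High: 0.3 × 0.4 + 0.7 × 0.05 = 0.155, or 15.5%

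Share over 75 among the invited = *p*(1 − *a*) / [*p*(1 − *a*) + (1 − *p*)(1 − *b*)]

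| *p* | *a*, *b* | Calculation | Share among invited |
|---|---|---|---|
| 20% | 20%, 5% | 0.16 / (0.16 + 0.76) | 17.4% |
| 20% | 40%, 2% | 0.12 / (0.12 + 0.784) | 13.3% |
| 30% | 20%, 5% | 0.24 / (0.24 + 0.665) | 26.5% |
| 30% | 40%, 2% | 0.18 / (0.18 + 0.686) | 20.8% |

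For scale, the standard error of a 20% share at n = 100 is √(0.2 × 0.8 / 100) = 4 percentage points. The mildest shift (20% to 17.4%) is smaller than that; the largest (30% to 20.8%) is about twice it.

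**The case against.** The case for leaving the plan as it is has several parts.

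- **The bias is disclosed.** This is correct. The article names it, and its limitations list adds that results may not generalise. A reader might infer that the bias was hidden; it was not. What remains is that it is left in place although existing procedures could largely remove it.
- **The loss can be seen.** A reader might infer that unreached patients vanish without trace. That goes too far: Table 1 counts possible participants per week, and Statistical analysis describes attrition at various stages with reasons. A gap between possible and asked could therefore show. Neither item is said to record the mode of contact or the reason a patient was not asked.
- **Exclusion is inferred.** The article nowhere says that patients without email or mobile are skipped, and it condenses a full protocol whose flow chart is not shown. A fallback may exist there. Against this, Sources of bias states the email or text approach for all potentially eligible patients and concedes the bias that follows.
- **The link to risk is indirect.** The Introduction reports associations among several factors. It does not rank older or deprived patients as the highest-risk groups, and it does not link age or deprivation to lacking a mobile number. A text needs only a mobile phone, and every invitee is then spoken to. The overlap is plausible but not documented.
- **A posted leaflet could miss the ten-day window.** This stands, and the fix allows for it.

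**Conclusion.** The point holds as a low-cost improvement to a disclosed weakness. As described, email or text is the sole entry, and eligible patients with neither have no stated way in, which sits badly with seeking consent from all eligible patients and with the non-digital consent route. They are also outside the denominator of the uptake measure.

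The size is unknown. The range of about 6% to 16% never invited rests wholly on assumed inputs and should not be read as an estimate for this population; at its lower end the effect on case mix would be lost in sampling error. The documents do not support a claim that the 91-day opioid results are biased by any particular amount, or that the groups at greatest risk are shut out. They support only that older or deprived patients may be under-represented, and that the study as described would not say by how much. No sample size figure changes.

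**What to change.** In the Recruitment section:

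1. Where no email address or mobile number is held, or the message fails, the practice telephones directly in the same time frame and gives the full explanation verbally. A paper leaflet is provided at or before the first appointment, and posted only if the ten-day window allows.
2. Bring the online-only consent wording into line with the Consent process section, so that completion with the pharmacist is available in both places.
3. Log the mode of approach for each patient.
4. Report the number of eligible patients not reachable digitally, and uptake by mode of approach and by age.

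If the full protocol already contains such a fallback, state it in the article and correct Sources of bias to match.

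The cost is a few minutes of practice time per such patient, printing or postage, and a minor amendment.

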### Consent process

Consent to participate in the study will be sought from all
eligible patients that have undergone a surgical procedure and are discharged with an opioid prescription from the participating East Kent hospital sites and participating GP practices. Consent will only be sought after a full explanation and/or the PIL has been offered with time allowed for questions and proper consideration. Individuals willing to take part and for whom an MUR appointment has been made will be asked to complete a Participant Consent Form. A Consent form will be sent to those with digital capabilities prior to the MUR or completed together with the pharmacist at the first appointment. A typewritten signature or tick box declaration option, in accordance with the UK eIDAS Regulations (SI 2016/696) will be used for all digital consent forms. All consent forms will be checked and countersigned by the pharmacist prior to the commencement of the medication review. A copy of the consent form will be added to the participants medical records, and another retained in the study site folder, stored at the practice and a copy sent to the participant.

### Study interventions

Following recruitment and consent of eligible participants, a timely appointment (within ten days of hospital discharge) will be arranged with the pharmacist for an opioid MUR and biopsychosocial assessment. A detailed schedule of events can be found in
Table 2.

**Table 2. T2:** Participant timeline and schedule of events.

			Follow-up			
Study activity	Pre-intervention	Baseline (Day 0)	Day 14 (± 3 days)	Day 31 (± 5 days)	Month 3 (± 7 days)	Post- intervention
Eligibility check by Health Care Professional	**☑**	**☑**				
Informed consent	**☑**	**☑**				
Demographics		**☑**				
EQ5D-5L		**☑**	** ☑ ^ a ^ **	** ☑ ^ a ^ **	** ☑ ^ a ^ **	
Pain Score		**☑**	**☑**	**☑**	**☑**	
MUR		** ☑ ^ b ^ **	** ☑ ^ b ^ **	** ☑ ^ b ^ **	**☑**	
De-escalation pathway agreed		**☑**	**☑**	**☑**	**☑**	
Medication change form and prescription if required.		**☑**	**☑**	**☑**	**☑**	
Data Collection		**☑**	**☑**	**☑**	**☑**	
Participant experience questionnaire			**☑ ^ a ^ **	**☑ ^ a ^ **	**☑ ^ a ^ **	
Participant interview invite			**☑ ^ a ^ **	**☑ ^ a ^ **	**☑ ^ a ^ **	
Handover /discharge to standard care or pain clinic					**☑**	
Participant interview						**☑**

^
**a**
^Activities occurring at participants final appointment as determined by their individual de-escalation plans.
**
^b^
**Optional follow-up appointments may be agreed depending on de-escalation plan and individual needs. Abbreviations: EQ5D-5L - European Quality of Life 5 Dimension 5 Level; MUR – medicines use review.

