### Aims and objectives

The primary aim of this study is to evaluate a multi-centre, pharmacist-led, early opioid deprescribing intervention. This is designed for patients discharged following a surgical procedure with an opioid prescription from hospitals within a single NHS Trust in an area of high opioid prescribing, East Kent. It will determine whether this designed intervention is able to support early deprescribing of opioids in this particular healthcare setting and with this particular patient population and to inform a much larger, clinical trial. A summary of the aims and objectives for this study are collated in
Table 1.

**Table 1. T1:** Summary of study aims and objectives.

Aims/questions	Objectives
**To test the feasibility of delivering an early opioid ** **deprescribing intervention in primary care, led by ** **trained clinical pharmacists.**	**Ascertain stakeholder acceptability of the intervention:** • Maintain detailed records of any barriers or enablers that may occur in response to setting up the intervention and whilst delivering the intervention • Deliver stakeholder interviews
	**Measure the capabilities of trained clinical pharmacists to deliver an ** **early opioid medication review by**: • Completed intervention delivery training • Observational competency checks by Clinical Lead • Completed medication review case reports • Number of participants successfully deescalated
	**Ascertain participant acceptability of the intervention by measuring**: • Number of participants that enrol in the study • Number of withdrawals from the study • Adherence to pharmacist medication recommendations • Responses to participant satisfaction questionnaire • Responses during participant interviews
	**Apply a micro-costing approach to estimate the intervention costs:** • opioid medication costs • staff costs • Health resource use (primary care services, community-based services, hospital inpatient and outpatient services)
**To measure successful discontinuation and/or ** **reduction in the use of opioids to within the ** **recommended 2–4-week period for opioid use ** **or by the expected period of tissue healing (<91 ** **days) whichever is sooner ^ 39 ^.**	**Measurement of** the mean difference in morphine milligram equivalent (MME) dose at baseline and at 90 days

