### Data collection

Data variables collected pre-intervention or on day 0 will include baseline demographics, pain scores, EQ5D-5L (Quality of Life Questionnaire), and a number of key confounders that have been reported in the literature, and linked to long-term opioid use:

Baseline demographics (age, sex, body mass index (BMI), ethnicity, social deprivation scores, smoking and alcohol consumption).Surgical history (surgery type, hospital, ward, opioid – type, strength, duration, average pain score).Medical history (prior opioid use, prior gabapentinoid and psychotropic use, other medication use, comorbidities, healthcare use).

At each additional follow-up appointment data variables collected will include pain scores, further medication changes, symptom management and for final appointments only, EQ5D-5L and Participant Feedback Questionnaire data. The aim of this questionnaire is to ascertain their experience of the deprescribing intervention, their views, and opinions on the process. In addition, all participants will be invited to take part in an online or telephone interview after their final follow-up with the pharmacist.

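### The experience questionnaire and interview invitation are scheduled only at or after the final appointment, so two of the five acceptability measures are not set up to hear from early leavers

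*Protocol article*

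**What the plan says.** Table 2 (Study interventions) ticks the participant experience questionnaire and the interview invitation at Day 14, Day 31 and Month 3, and not at baseline. Every one of those ticks carries footnote a: "Activities occurring at participants final appointment as determined by their individual de-escalation plans". The Data collection section agrees. The questionnaire is collected "for final appointments only, EQ5D-5L and Participant Feedback Questionnaire data", and the interview is described as "all participants will be invited to take part in an online or telephone interview after their final follow-up with the pharmacist".

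The End of intervention section gives two end points: opioids stopped with the final paperwork done, or three months reached. Withdrawal is not one of them.

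Table 1 (Aims and objectives) lists five measures of participant acceptability. Three are enrolment ("Number of participants that enrol in the study"), withdrawals ("Number of withdrawals from the study") and adherence ("Adherence to pharmacist medication recommendations"). The other two are the questionnaire ("Responses to participant satisfaction questionnaire") and the participant interviews. Outcome 3 in Table 3 is barriers and enablers as seen by the surgical patient. The sample size paragraph says that the planned 80 to 100 "will allow for participant loss, to follow-up", without giving a rate.

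**The concern.** People who leave early are a group in whom the intervention may well have been unacceptable or impractical. If the two instruments that record the patient's own view are issued only at an appointment that leavers do not reach, satisfaction and patient-reported barriers are conditional on having stayed. The result could look better than the experience of everyone enrolled, and the barriers that lead to drop-out could be under-reported. Feasibility is the study's primary outcome and the results are meant to shape a larger trial, so a barrier that goes unheard here could be carried into that trial's design.

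The text also pulls two ways. It promises an interview invitation to everyone and then fixes a time that some participants will not reach.

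**Working it through.** **Step 1: who triggers each instrument.** The rules in Table 2 footnote a, Data collection and End of intervention, applied as written:

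- Opioids stopped by Day 14 or Day 31: that visit is the final appointment, and both instruments are issued.
- Still on opioids at three months: the Month 3 visit is final, and both are issued.
- Withdraws or stops attending before the planned final visit: no final appointment takes place, and neither instrument is scheduled. The last visit attended cannot stand in for it, because the footnote defines the final appointment by the de-escalation plan, and nobody knows at the time that an attended visit will prove to be the last.

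**Step 2: which acceptability measures are affected.** Of the five in Table 1:

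| Measure | Depends on reaching the final appointment? |
|---|---|
| Enrolment | No |
| Withdrawals | No; counts leavers directly |
| Adherence to recommendations | No |
| Questionnaire | Yes |
| Interviews | Yes |

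The Statistical analysis section also describes attrition by stage with the reasons given, and compares those who accepted with those who declined. The restriction therefore falls on two of five measures, and through them on Table 3 outcome 3.

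**Step 3: how much it could matter.** The article states no attrition rate and no satisfaction rate, so there is no figure to reproduce. What follows is illustration.

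Inputs: recruitment of 80 to 100 and a benchmark of 70 (Recruitment, sample size). The room for loss is d = 1 − 70/N.

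- N = 80: d = 1 − 70/80 = 12.5%.
- N = 100: d = 1 − 70/100 = 30%.

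This is headroom over the benchmark, used here as an assumed loss. It is not a forecast of attrition.

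Let p be the proportion satisfied among those who reach the final appointment, all of whom are taken to respond. With nothing known about leavers, the all-participant proportion lies between p(1 − d), if no leaver is satisfied, and p(1 − d) + d, if every leaver is.

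| Assumed p | Assumed d | Lower bound | Upper bound |
|---|---|---|---|
| 90% | 12.5% | 0.90 × 0.875 = 78.8% | 0.7875 + 0.125 = 91.3% |
| 90% | 30% | 0.90 × 0.70 = 63.0% | 0.63 + 0.30 = 93.0% |
| 80% | 12.5% | 0.80 × 0.875 = 70.0% | 0.70 + 0.125 = 82.5% |
| 80% | 30% | 0.80 × 0.70 = 56.0% | 0.56 + 0.30 = 86.0% |

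The observed p lies inside every interval, so the direction of the error is not determined by the arithmetic. The possible overstatement is larger than the possible understatement: at p = 90% and d = 30% it is 27 points against 3.

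**The case against.** A reader might infer that acceptability is measured in completers only and that leavers are never asked anything. The article does not support that. Withdrawal is itself a named acceptability measure, so leaving does count as a negative signal. Enrolment and adherence do not depend on the final appointment. Reasons for attrition are to be described, and pharmacists' notes from each review meeting are to be examined for themes, which would include visits made before someone left. Those notes are aimed at recommendations for the intervention and at the pharmacist's role, however, and do not replace the patient's own account.

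Nor is the surveyed group limited to successes. Patients who do not want to stop opioids can be placed on Pathway C and kept under review, and those still on opioids at 91 days reach the end of the intervention. The filter is staying in the study, not stopping opioids.

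It can also be said that this is a condensed article, that the flow chart is not reproduced, and that a withdrawal procedure may sit in the full protocol. That is fair, and it rules out certainty that leavers receive nothing. It does not remove the point, because the article does more than stay silent: it states that the questionnaire belongs to final appointments only. A withdrawal procedure that offered the questionnaire would contradict that sentence.

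Finally, the article sets no satisfaction percentage as an endpoint, and interviews are analysed thematically. The percentages above therefore show scale and do not correct any planned estimate.

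**Conclusion.** The point holds for the questionnaire and the interviews, not for acceptability as a whole. As written, these two measures are scheduled only for people who reach or pass the final appointment, and the promise to invite all participants to interview conflicts with that timing. The patient-perspective evidence may be too favourable and may miss causes of drop-out. An upward bias is plausible but not shown, and its size cannot be stated from the article. The intervals above rest on assumed satisfaction of 80% or 90%, assumed losses of 12.5% or 30%, and full response among those who stay. No power or safety statement depends on this, but Table 3 outcome 3 does, and the change is inexpensive, so it should be made.

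**What to change.** Amend Table 2 footnote a and the Data collection text so that the questionnaire and the interview invitation are offered at the final appointment, at withdrawal, or after a missed final appointment, whichever comes first. Use the email or text route already in place for recruitment, and leave out anyone who declines further contact. This also reconciles the invitation to all participants with its timing.

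Report the number of responders out of all enrolled. Give satisfaction among responders separately for completers and leavers. Do not use all enrolled as the denominator for satisfaction itself, since that would count non-response as dissatisfaction.

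The cost is a protocol amendment that may need ethics review and a few extra messages. Response among leavers is likely to be low, so their results may rest on small numbers. At the stated status date in July 2024, 18 participants had been recruited and one interview done, so most of the planned data were still to be collected.
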